In one retrospective study, the sagittal balance parameters of the spine and pelvis as shown by lumbar vertebral magnetic resonance imaging (MRI) and X-ray examination were compared between 32 patients aged >50 years with LDH at L4/5 and L5/S1 and 32 asymptomatic healthy persons.^[11]^ The study showed that the degree of lumbar lordosis was smaller in patients with LDH (−43.52 ± 14.56 degrees in the LDH group and −48.3 ± 11.1 degrees in the normal group). The pelvic incidence (PI) was also smaller in patients with LDH (45.1 ± 9.6 degrees in the LDH group and 49.12 ± 10.02 degrees in the normal group). The sacral slope (SS) was smaller in patients with LDH (32.05 ± 9.40 degrees in the LDH group and 34.8 ± 7.8 degrees in the normal group), as was the pelvic tilt (PT) (10.3 ± 6.7 degrees in the LDH group and 17.53 ± 8.57 degrees in the normal group). The severity of thoracic kyphosis was greater in patients with LDH (27.6 ± 10.33 degrees in the LDH group and 24.2 ± 9.8 degrees in the normal group). At present, there is a lack of research on the parameters of spinal sagittal balance and lumbar bone structure in elderly patients with complicated LDH treated by spinal balance manipulation combined with Daoyin therapy. The above research results provide an important theoretical basis for the development of our current project, which is also a continuation of previous work. Pelvic traction is beneficial for alleviating the symptoms of nerve root compression and is a common method for treating LDH. There is no clear clinical evidence against the use of traction in the treatment of LDH. Therefore, patients in the control group of our proposed study will be mainly treated with pelvic traction.

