### Randomization and allocation

2.10

After screening, the patients will be randomly divided into 2 groups at a 1:1 ratio. Randomization will be performed using random numbers generated by SPSS version 21.0 (IBM Corp., Armonk, NY, USA). The patients will be randomly divided into a treatment group (n = 36) and control group (n = 36), and the group assignment will be concealed from the researchers by a senior data manager who will not be involved in the study. The group assignments will be sealed in opaque envelopes and be opened by the researchers following acquisition of informed consent and completion of baseline testing.

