### Data collection and monitoring

2.12

This is a 24-week clinical trial in which the participants will undergo the research intervention for 4 weeks with a 24-week follow-up. The primary outcome measures will be assessed at 5 time points (at baseline and at weeks 2, 4, 12, and 24), the secondary outcome measures will be assessed at 2 time points (at baseline and at week 24), and safety will be assessed at 6 time points (at baseline and at weeks 1, 2, 4, 12, and 24). All results will be independently documented by 2 investigators using EpiData version 3.1 (EpiData Association, Odense, Denmark), and differences will be resolved through discussion with a third investigator. The Longhua Hospital Affiliated to Shanghai University of Traditional Chinese Medicine will be responsible for monitoring and quality control.

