### Statistical analyses

2.13

Trained statisticians will use the intentionality approach for validity assessment and safety analysis. The final outcome observation method will be applied to deal with missing values. All statistical analyses will be performed using SPSS version 22.0 (IBM Corp.). Before randomization, the patients baseline characteristics will be collected as descriptive statistics, including sex, age, body mass index, duration of symptoms, and degree of LDH. The data analysis of the primary outcome will be based on the per-protocol population as a supportive analysis. The mean, standard deviation, median, quartiles, and interquartile ranges will be calculated for continuous variables, and the frequency will be calculated for categorical variables. Continuous variables with a normal distribution will be calculated by the independent-samples Student *t* test and presented as mean with standard deviation; otherwise, the data will be analyzed using non-parametric tests and expressed as median with range.

Categorical variables will be expressed as number (%) and analyzed by the χ^2^ test or Fisher exact test. Repeated-measures analysis of variance will be used to analyze the changes in the VAS score, PPT, and ODI score at different time points (baseline and weeks 1, 2, 4, 12, and 24). An independent-samples *t* test will be used to analyze the changes in lumbar lordosis, lumbar vertebral angle, tilt angle of the first thoracic vertebra line, PI, PT, SS, and LM at baseline and 24 weeks. A *P* value of <.05 will be defined as statistically significant, and two-sided 90% confidence intervals will be calculated. Missing data will be input with the last observed response carried forward for all measures using the “last-value-carried-forward” principle.

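### The secondary imaging outcomes are compared by a t test on change without baseline as a covariate: valid, but less precise than ANCOVA on the same data

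*Protocol article*

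**What the plan says.** Section 2.13 (Statistical analyses) assigns one method to seven imaging parameters: an independent-samples t "test will be used to analyze the changes in lumbar lordosis, lumbar vertebral angle", the tilt angle, and "PI, PT, SS, and LM at baseline and 24 weeks". The general rule in the same section is also unadjusted: "Continuous variables with a normal distribution will be calculated by the independent-samples Student" t test, with non-parametric tests otherwise. No baseline covariate or adjusted model appears anywhere in the article.

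The data for an adjusted analysis will exist. Section 2.12 (Data collection and monitoring) states that "the secondary outcome measures will be assessed at 2 time points (at baseline and at week 24".

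Section 2.10 (Randomization and allocation) describes simple 1:1 allocation: "The patients will be randomly divided into a treatment group (n = 36) and control group (n = 36". It mentions no stratification, so balance on the imaging baselines is left to chance.

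**The concern.** A t test on change subtracts the whole baseline value from the week-24 value, as if each extra degree at baseline predicted exactly one extra degree at week 24. When r is below 1 (with similar spread at both visits), the true slope is smaller. Two things follow. The change score carries avoidable noise. It also over-corrects: if one arm happens to start higher, the estimated effect is pushed in the opposite direction by (1−r) times the baseline difference, which can resemble a treatment effect or mask one.

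The imaging outcomes are secondary, but the Discussion gives the effect on sagittal balance and lumbar structure as one of the things the trial will explore. With about 30 evaluable patients per arm, precision is limited. Because the article names the test, this concerns a method it has fixed, not a detail left for a later document.

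The wording is also loose. Changes tested at baseline and at 24 weeks most naturally means change scores, but the phrase could describe a separate t test at each time point.

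**Working it through.** **The plan's own figure.** The article states no power or sample size for the imaging outcomes. Its only calculation (section 2.9) is for a rate. With p = (0.920 + 0.866)/2 = 0.893 and a margin of 0.2, 12.365 × 0.893 × 0.107 / 0.04 = 29.537, or 30 per arm. This reproduces the stated figure and does not depend on how the imaging is analysed.

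**Inputs.**
- 36 randomized per arm (section 2.10); 30 per arm before the allowance for loss (section 2.9).
- SD of lumbar lordosis 14.56 degrees, from the retrospective comparison in the Introduction: "43.52 ± 14.56 degrees in the LDH group". Used for illustration only.
- Two-sided 5% level and 80% power, assumed for the illustration (section 2.13 sets P < .05).
- r is **not given**; 0.5, 0.7 and 0.9 are assumed.
- Equal SDs at the two visits and a common slope in both arms are assumed.

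**Variance.** Per patient, in units of SD²:
- change score: 2(1−r)
- ANCOVA: 1−r²
- ratio: (1−r²)/[2(1−r)] = (1+r)/2

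Estimating the slope multiplies the ANCOVA variance by 1 + 1/(2n−4). With n = 30 this is 1 + 1/56 = 1.018.

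**Detectable difference.** (1.960 + 0.842) × √(2/30) × 14.56 = 10.53 degrees, multiplied by √[2(1−r)] for the change score and √(1−r²) for ANCOVA.

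| Assumed r | Ratio (1+r)/2 | Ratio with slope estimated | Change score, degrees | ANCOVA, degrees | ANCOVA, slope estimated |
|---|---|---|---|---|---|
| 0.5 | 0.75 | 0.76 | 10.5 | 9.1 | 9.2 |
| 0.7 | 0.85 | 0.87 | 8.2 | 7.5 | 7.6 |
| 0.9 | 0.95 | 0.97 | 4.7 | 4.6 | 4.6 |

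Allowing for slope estimation, where the change-score test has 80% power ANCOVA has about 89%, 85% and 81% at these three values of r.

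**Chance imbalance.** With 30 per arm, the SD of the baseline difference in lumbar lordosis is 14.56 × √(2/30) = 3.76 degrees. The change-score estimate retains −(1−r) of the observed difference, so a one-SD imbalance shifts it by:
- r = 0.5: 0.5 × 3.76 = 1.9 degrees
- r = 0.7: 0.3 × 3.76 = 1.1 degrees
- r = 0.9: 0.1 × 3.76 = 0.4 degrees

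For scale, the Introduction's gap in mean lordosis between patients and healthy persons is 48.3 − 43.52 = 4.8 degrees. ANCOVA leaves about none of the imbalance in the estimate.

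**Simulation check.** In 20,000 simulated trials with 30 per arm, the variance ratios at r = 0.5, 0.8 and 0.9 were 0.77, 0.91 and 0.97. The slope of the change-score estimate on the baseline difference was −0.50, −0.21 and −0.10, in line with the formulas.

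**If the test is run on week-24 values alone.** The ANCOVA variance is then 1−r² of the t-test variance: 0.75, 0.51 and 0.19 at r = 0.5, 0.7 and 0.9, and the t-test estimate retains +r of the imbalance.

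**The case against.** The strongest reply is that this is a preference about efficiency and not an error. That stands in large part. Over randomization, a t test on change is unbiased and keeps its type I error. The outcomes are secondary, and no power is claimed for them.

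The gain also depends on a correlation that the article does not give, and there are reasons to think it may be high for some parameters. Section 2.7.2.3 itself describes pelvic incidence as fairly constant. Section 2.13 carries the last value forward; with imaging only at baseline and week 24, a patient without week-24 imaging would contribute the baseline value twice, which raises the analysed correlation. With 20% loss and equal means and variances, an underlying 0.7 becomes 0.8 × 0.7 + 0.2 × 1 = 0.76. At r = 0.9 the gain for lumbar lordosis is only about 0.1 degree.

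Three stronger readings are tempting, and the article does not support them:
- *That chance baseline imbalance is ignored.* A change score does use the baseline, with a slope of 1 instead of an estimated slope. What remains is −(1−r) of the difference, which is small when r is high.
- *That the large spread in lordosis makes imbalance likely.* The SD sets the size of an imbalance in degrees. In standardized terms, imbalance depends on the number of patients. The 14.56 also comes from 32 patients aged over 50, whereas this trial enrols ages 40 to 75.
- *That the loss is of the order of the week-24 ratios (0.51 or 0.19).* Those apply only if the test ignores baseline, which is the less natural reading of a sentence about changes.

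The reply does not show that the stated test should be kept. Apart from the small cost of estimating one slope, ANCOVA is never less precise, whatever r turns out to be. Not knowing r therefore favours ANCOVA.

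**Conclusion.** The point holds as a matter of efficiency and clarity. Section 2.13 fixes a valid test that over-corrects for baseline and uses the data less well than ANCOVA would. On the change-score reading, with 30 per arm and the slope estimated, ANCOVA reduces the variance by about 24% at r = 0.5, 13% at r = 0.7 and 3% at r = 0.9. The loss is larger if the test is meant for week-24 values alone, and the text should rule that reading out.

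These sizes rest on assumed correlations, equal SDs at the two visits and, for the figures in degrees, an SD from a different sample. The formula (1+r)/2 does not depend on that SD. Nothing here invalidates the planned comparison or bears on the primary outcomes or the 72 patients.

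**What to change.** In section 2.13, replace the independent-samples t test for each imaging parameter with ANCOVA: week-24 value as outcome, treatment group as factor, the patient's own baseline value as covariate. Report the adjusted between-group difference with its confidence interval. In the same sentence, state that the comparison is between arms at week 24, and say whether the non-parametric fallback still applies to these parameters.

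The cost is a change of wording. Both measurements are already scheduled, the SPSS software named in the plan fits the model, and the stated sample size is unaffected.

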### Sample size calculation

2.9

We estimated the sample size based on the main outcome indicators, and we conducted a randomized trial of Shi-style lumbar spine manipulation combined with Daoyin therapy versus lumbar traction from March to September 2018, with 10 participants in each group. The outcome parameter was the rate of improvement in the NDI (neck disability index) score from baseline to the end of the 8-week treatment. The results showed that the rate of improvement after Shi-based lumbar spine manipulation combined with Daoyin therapy was 92.0%, while that after lumbar traction was 86.6% (*P* = .893) (α = 0.05, test efficiency 1 − β = 0.8, and equivalent standard δ = 0.2).

Because our study protocol will involve the use of a non-inferiority test, according to the number of cases in the clinical non-inferiority and equivalent tests and the equivalent standard,^[17]^ and using counting data (rates) as the outcome indicators, the following formula was used to estimate the number of patients required for this study:$$n=2\times {\left({\text{U}}_{\alpha }+{\text{U}}_{\beta }\right)}^{2}\times \text{p}(1-\text{p})/\delta^{2}$$

2 × (U_α_+ U_β_)^2^was calculated as 12.365, and N was 29.537 after substituting the above figures, and the sample size of each group was about 30 cases; according to the loss rate of 20%, the sample size of each group was 36 cases, and the ratio of treatment group and control group was 1:1, a total of 72 cases.

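### Section 2.13 pairs one blanket P < .05 with one blanket two-sided 90% interval for tests of difference, and names no non-inferiority comparison to which the 90% interval could belong

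*Protocol article*

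**What the plan says.** Section 2.13 (Statistical analyses) gives one threshold and one interval level, and ties neither to a particular analysis: "A *P* value of <.05 will be defined as statistically significant, and two-sided 90% confidence intervals will be calculated". The term two-sided is attached to the interval only; the sidedness of P is not stated.

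The methods named in the same section are:

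- Primary outcomes: "Repeated-measures analysis of variance will be used to analyze the changes in the VAS score, PPT, and ODI score at different time points".
- Imaging outcomes: "An independent-samples *t* test will be used to analyze the changes in lumbar lordosis, lumbar vertebral angle", and the further spinal, pelvic and muscularity parameters listed with these.
- Categorical data: "Categorical variables will be expressed as number (%) and analyzed by the χ^2^ test or Fisher exact test".
- Non-parametric tests where a continuous variable is not normally distributed.

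Section 2.9 (Sample size calculation) states a different inferential aim: "Because our study protocol will involve the use of a non-inferiority test". Its inputs are "α = 0.05, test efficiency 1 − β = 0.8, and equivalent standard δ = 0.2", again without sidedness, and its result is that the multiplier "was calculated as 12.365, and N was 29.537 after substituting the above figures".

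**The concern.** All the methods in 2.13 ask whether the groups, or the time courses, differ. A test of difference at two-sided 5% corresponds to a 95% interval; a two-sided 90% interval corresponds to a two-sided 10% test, or a one-sided 5% test. Section 2.13 puts the two side by side without saying which analysis each serves.

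The 90% level has a plausible source in the non-inferiority design of 2.9. The analysis section never makes that link. It describes no non-inferiority test, and no interval bound is compared with a margin. As written, the 90% interval can only attach to estimates of difference, where the natural reference value is zero. A borderline difference in pain, disability or an imaging parameter could then be reported as non-significant beside an interval that excludes zero. All difference estimates would also look more precise than the stated significance level implies.

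**Working it through.** **Inputs.** From 2.9: improvement rates 92.0% and 86.6%, alpha 0.05, power 0.80, margin 0.2, multiplier 12.365, n = 29.537 per group, rising to 36 per group after the allowance for loss. From 2.13: P < .05 and two-sided 90% intervals.

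**Step 1: which alpha does 2.9 use?** The formula is n = 2(z_α + z_β)² p(1 − p)/δ², with p = (0.920 + 0.866)/2 = 0.893, so p(1 − p) = 0.893 × 0.107 = 0.09555.

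- One-sided 5%: 2(1.6449 + 0.8416)² = 12.365, and n = 12.365 × 0.09555/0.04 = 29.54. Both figures match the document.
- Two-sided 5% (one-sided 2.5%): 2(1.9600 + 0.8416)² = 15.698, and n = 15.698 × 0.09555/0.04 = 37.50. Neither matches.

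The alpha in 2.9 is therefore one-sided 5%. Its companion is a two-sided 90% interval, with the relevant bound compared with the margin of 0.2 and not with zero.

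**Step 2: which interval matches the tests in 2.13?** Take an independent-samples t test with 36 per arm, so df = 2 × 36 − 2 = 70.

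- 90% interval: difference ± 1.667 SE.
- 95% interval: difference ± 1.994 SE.
- Width ratio: 1.667/1.994 = 0.836, so the 90% interval is about 16% narrower. Conversely 1/0.836 = 1.196, so the 95% interval is about 20% wider.

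**Step 3: where do P and the interval disagree?** They disagree for 1.667 < |t| < 1.994, that is, two-sided P between .05 and .10. Multiplying by √(2/36) = 0.2357 gives observed standardised differences of about 0.39 to 0.47.

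Example, t = 1.80: two-sided P = .076. In SE units the 90% interval is 1.80 ± 1.667 = 0.13 to 3.47, which excludes zero. The 95% interval is 1.80 ± 1.994 = −0.19 to 3.79, which includes it.

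**Step 4: how often?** With no true effect, the probability of two-sided P between .05 and .10 is 0.10 − 0.05 = 5%. From the noncentral t distribution with 70 df, the probability peaks at 12.8%, at a noncentrality of about 1.85.

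**Step 5: could P be one-sided?** For t = 1.80 the one-sided P is .038, which agrees with the 90% interval, so that reading would reconcile a t test. It does not reach the primary outcomes, which 2.13 assigns to repeated-measures ANOVA, or the categorical data. The F test and the chi-square test are non-directional.

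**The case against.** The strongest defence is that the 90% interval is no mistake: it is the standard companion to the one-sided 5% non-inferiority test for which 2.9 sized the trial. That stands. A reader might infer that 90% is simply the wrong level and should become 95% throughout. The documents do not support this. For a non-inferiority comparison the bound is judged against the margin, so excluding zero is not the criterion and the conflict in Step 3 does not arise. Moving that comparison to a 95% interval would also require 37.5, that is 38, per group before loss, against the plan's 30.

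Second, 2.13 defines significance by P alone and gives the interval no decision role. That also stands. A reader might infer that the trial runs a 10% false-positive rate; this is so only if someone uses the intervals as tests, which the plan does not say.

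Third, a reader might infer that the planned 80% power is overstated because 2.13 tests at two-sided 5%. The power in 2.9 belongs to a non-inferiority test on an improvement rate. Recomputing it at one-sided 2.5% describes an analysis that nobody planned, and says nothing about the power of the difference tests on VAS, PPT, ODI or imaging.

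Fourth, an article may leave the pairing of tests and intervals to a fuller analysis plan. That would excuse silence. Here the article states a general rule, and as stated the rule does not suit the tests that it governs.

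**Conclusion.** The point holds in a limited form. Section 2.13 gives estimates of difference an interval level that does not match a two-sided 5% test, and never connects the 90% interval to the non-inferiority comparison in 2.9 that would justify it. The effect is on borderline results and on presentation: conflicting readings in a band reached 5% of the time under no effect and at most about 13% otherwise, and intervals about 16% too narrow for the test beside them.

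This rests on reading P as two-sided, which the article does not state but which the non-directional ANOVA and chi-square tests imply. The |t| band applies to a two-sample t test with all 36 per arm analysed. For the ANOVA it is a guide only, applying to single between-group contrasts.

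**What to change.** In 2.13:

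- State that tests of difference are two-sided at 5% and that their estimates are reported with 95% intervals.
- Name the non-inferiority comparison that 2.9 says will be made, including its outcome. Reserve the two-sided 90% interval for it, and state that the relevant bound is judged against the margin of 0.2 at one-sided 5%. That margin is set in 2.9 on a rate of improvement, so the text should say which trial outcome supplies the rate.

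In 2.9, label alpha = 0.05 as one-sided beside the multiplier 12.365, so that the 80% power is not read as belonging to the difference tests.

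The cost is wording in two sections. Difference intervals become about 20% wider. The sample size of 72 is unchanged, because the non-inferiority comparison keeps its one-sided 5% level.

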## Method/design

2

The purpose of this prospective randomized controlled clinical trial is to investigate whether Shi-style spine manipulation combined with Daoyin therapy can lead to improvements in middle-aged and elderly patients with LDH. The study will be conducted in the Department of Orthopaedics, Longhua Hospital, Shanghai University of Traditional Chinese Medicine. The principal investigator will be responsible for the entire project, including organization of the steering committee meetings. An independent steering committee will be responsible for participant safety, meetings, participant recruitment, and quality control. The coordination center will be responsible for communicating protocol modifications and providing materials. The trial will involve 4 weeks of treatment and 6 months of follow-up. After randomization, the patients will receive one course of treatment within 4 weeks. The results will be evaluated at baseline and at weeks 2, 4, 12, and 24.

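### Carry-forward is the only missing-data rule, and the efficacy ANOVA lists a week 1 that is not scheduled: lost patients' imaging change becomes zero and group differences can be biased in either direction

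*Protocol article*

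**What the plan says.** All references are to the protocol article.

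- **Missing data** (Statistical analyses): "Missing data will be input with the last observed response carried forward for all measures". The section gives no other method and no sensitivity analysis for missing data. Its supportive per-protocol analysis does not address the rule.
- **Primary outcomes, analysis** (Statistical analyses): "Repeated-measures analysis of variance will be used to analyze the changes in the VAS score, PPT, and ODI score at different time points", with the levels given as "baseline and weeks 1, 2, 4, 12, and 24". Baseline is therefore a level of the repeated factor. The section does not say whether the group main effect or the group-by-time interaction is the test.
- **Primary outcomes, schedule** (Data collection and monitoring): "The primary outcome measures will be assessed at 5 time points (at baseline and at weeks 2, 4, 12, and 24". The Abstract and Method/design agree; the latter has "The results will be evaluated at baseline and at weeks 2, 4, 12, and 24".
- **Week 1** appears in the schedule only for safety: "safety will be assessed at 6 time points (at baseline and at weeks 1, 2, 4, 12, and 24".
- **Imaging** (Data collection and monitoring): "the secondary outcome measures will be assessed at 2 time points (at baseline and at week 24". Changes are compared by t test.
- **Loss**: Sample size calculation allows 20% and enrols 36 per group. It frames the trial as non-inferiority.

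**The concern.** Carrying the last value forward assumes that a patient who leaves would have stayed where last seen. In a condition where both arms are expected to improve, that assumption is usually false. It treats loss as lack of improvement, so an arm that loses more patients looks worse whatever its treatment does. Imputed values are also counted as observed, which misstates precision.

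Unequal loss is plausible here. Patients know their treatment, and the burdens differ: under Intervention, the treatment group exercises every other day for 6 months, while traction ends after 4 weeks.

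The non-inferiority framing adds to the problem. In a superiority trial, shrinkage towards zero is at least cautious. In a non-inferiority trial, it can make a worse treatment look acceptable.

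The week-1 mismatch is a second, smaller matter: the efficacy analysis names a visit for which no scores are planned.

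**Working it through.** **1. The plan's own figures.** Mean pilot rate (0.920 + 0.866)/2 = 0.893. n = 12.365 × 0.893 × 0.107 / 0.2² = 29.537, so 30 per group, and 30 × 1.2 = 36. These reproduce. With 20% loss, 36 × 0.8 = 28.8, or about 29 per group, is observed to the end.

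**2. Imaging: bias.** Let m be the mean change common to both arms, Δ the true extra change on treatment, and pT and pC the loss in each arm, unrelated to outcome. Lost patients count as zero change, so the expected difference is

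(1 − pT)(m + Δ) − (1 − pC)m = (1 − pT)Δ + (pC − pT)m.

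- Equal loss of 20%: 0.8Δ, which is 80% of the truth.
- No true effect, loss of 10% (treatment) versus 30% (control): 0.2m, a false difference. Swapping the losses reverses its sign.

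**3. Imaging: error rate and power.** Simulated t tests with 36 per arm, in units of the SD of change. The values of m, the 0.75 SD effect and the 10%/30% split are assumptions.

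| Common change m | False-positive rate, 10% vs 30% loss | Power for a 0.75 SD effect, 20% loss in each arm |
|---|---|---|
| 0 | 5% | 79% |
| 0.3 | 6% | 76% |
| 0.5 | 8% | not run |
| 1 | 14% | about 66% |

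The observed cases alone give 79% power.

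**4. Pain score: bias at week 24.** Simulated VAS with 36 per arm and 3,000 runs. Assumed: SD 2, correlation 0.5, control means 6, 4.5, 3.5, 3, 3 at baseline and weeks 2, 4, 12, 24. Dropout is either completely random (MCAR) or depends on the last score (MAR). Negative values favour treatment.

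| True effect | Loss, treatment/control | Carry-forward, MCAR | Carry-forward, MAR |
|---|---|---|---|
| 0 | 10%/30% | −0.28 | −0.42 |
| 0 | 30%/10% | +0.28 | +0.43 |
| −1 (constant) | 20%/20% | −0.93 | −1.02 |
| −1 (constant) | 10%/30% | −1.27 | −1.46 |
| −1 (constant) | 30%/10% | −0.64 | −0.58 |

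In the same settings, a baseline-adjusted mixed model on observed visits gave −0.99 to −1.02 when the truth was −1. It stayed within 0.01 of zero when the truth was zero.

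**5. Baseline as a level of the ANOVA.** An effect that is constant over the four real post-baseline visits and zero at baseline averages to 4/5 of itself in the group main effect. The group-by-time interaction is not diluted in this way.

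**6. Illustrative power.** Assumed: constant effect of 0.6 SD, correlation ρ = 0.5 between any two visits, 29 per arm, two-sided 5%, complete data.

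- Five-level group main effect: effect 0.8 × 0.6 = 0.48; variance of a patient's mean (1 + 4ρ)/5 = 0.60; SE √(2 × 0.60/29) = 0.203; ratio 2.36; power 64%.
- Baseline-adjusted contrast at one visit: variance 1 − ρ² = 0.75; SE √(2 × 0.75/29) = 0.227; ratio 2.64; power 74%.
- Baseline-adjusted average of four visits: variance (1 + 3ρ)/4 − ρ² = 0.375; SE √(2 × 0.375/29) = 0.161; ratio 3.73; power 96%.

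The same formulas at ρ = 0.3 give 77%, 65% and 95%; at ρ = 0.7 they give 54%, 88% and 99%.

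**The case against.** The other side has several good points.

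- **Week 1.** A reader might infer that every patient's week-1 score will be a copy of baseline, diluting a constant effect to 4/6. The documents do not support this. An unscheduled visit is not missing data, and the ANOVA's list of times is identical to the safety list. A copied list is far likelier. The mismatch still has to be reconciled.
- **Which ANOVA term.** The 4/5 dilution applies only to the group main effect. Analysing changes over time reads at least as naturally as the interaction, and the article names neither.
- **Power.** The 96% belongs to the four-visit average. It is not the gain from a single-visit contrast, which is 74% against 64% and falls below the main effect at correlation 0.3.
- **Imaging.** The documents give no data on change. They call pelvic incidence relatively constant, so a common change of 1 SD may be too large. With a small common change, the excess false positives and the loss of power nearly vanish. The 80% shrinkage under equal random loss remains.
- **Use of baseline.** The imaging t tests are on changes, so baseline is used by subtraction. ANCOVA is a gain in efficiency, not the repair of an error.

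A separate statistical analysis plan may exist, but that does not answer the point: the article does not leave the missing-data rule open, it fixes it. The core stands.

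**Conclusion.** The concern holds in this form: a single carry-forward rule applies to all measures with 20% loss planned, and the efficacy analysis lists a visit that the schedule does not collect. For imaging, the 80% shrinkage follows directly from the rule under equal random loss. The error rate under unequal loss runs from about 5% to 14%, depending on a common change and a loss split that the documents do not give, so 14% is the top of the range examined and not a forecast.

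For VAS, PPT and ODI, the safe statement is that bias can go either way. A reader might infer that carry-forward always shrinks the effect. The VAS simulation shows otherwise: it inflates the effect when the control arm loses more, and equal loss changed the week-24 estimate little (−0.93 to −1.02 for a true −1). Where shrinkage does occur, the non-inferiority framing means it is not conservative.

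This should be changed before analysis. The power comparisons are illustrations and do not carry the conclusion.

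**What to change.** 1. Reconcile the time points in Statistical analyses with Data collection and monitoring by removing week 1 from the efficacy analysis.
2. Analyse VAS, PPT and ODI with a mixed model for repeated measures on observed values at weeks 2, 4, 12 and 24. Include treatment, categorical visit, treatment-by-visit and the baseline score as covariate, with unstructured covariance and no imputation.
3. State the contrast to be reported: one named visit or the post-treatment average. The article names neither, and power depends heavily on the choice.
4. Analyse week-24 imaging by ANCOVA with the baseline value as covariate.
5. Keep carry-forward as a sensitivity analysis only. The mixed model is valid under missing at random, so add a sensitivity analysis for departures from it.

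The cost is analysis wording and a little programming. The planned SPSS software fits these models, and no patient, visit or measurement is added.
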